### Participants

Table 1 describes the inclusion/exclusion criteria for the trial. Prior to randomisation, potential participants are asked to provide documented verification (by a health professional, WL counsellor/friend, WL programme record booklet, diary or smartphone app or before/after photographs^47^) that they have achieved a clinically significant WL of >5% during the previous 12 months.

### Study recruitment

The study recruitment and intervention schedule is outlined in table 2. Centre-specific recruitment strategies were adopted for 12 months (March 2017–March 2018) and included commercial WL programme (UK, Slimming World); the Copenhagen Municipality weight management services, Dieticians from the Danish Association for Dieticians and commercial slimming companies (eg, Sense, Henrik Duer and Per Nielsen); registered clinical dieticians/nutritionists who provide weight management services in Lisbon; leisure centres; and local/national media coverage and advertisements. All participants were directed to country-specific recruitment websites (http://uk.nohow.eu; http://dk.nohow.eu; http://nohow.fmh.ulisboa.pt) and completed an online eligibility screener using Qualtrics. The eligibility screener categorised respondents as eligible, potentially eligible (wait-list) and ineligible. Eligible individuals were contacted for a telephone screening interview, provided with study information, medical history questions and the Physical Activity Readiness Questionnaire.^48^ Eligible participants were invited to a clinical investigation day (CID) where informed consent was obtained by research staff before randomisation (online supplementary file 1). Participants are reconsented before each subsequent visit and excluded if they become ineligible.

10.1136/bmjopen-2019-029425.supp1Supplementary data

**Table 2 T2:** Study recruitment and intervention schedule (Standard Protocol Items: Recommendations for Interventional Trials 2013 guidelines)

TIME POINT	Study duration				
	Recruitment	Baseline	6 months	12 months	18 months
	t_0_	t_1_	t_2_	t_3_	t_4_
RECRUITMENT					
Screening	X				
Informed consent		X			
Randomisation and allocation		X			
INTERVENTION					
Fitbit device training		X			
Intake24 (food diary) training		X			
Toolkit training (after randomisation)		X			
Arms 2–4 active intervention		♦———————♦			
Arms 2–4 follow-up			♦——————————————————♦		
Arm 1 (control) intervention		♦——————————————————————————♦			

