Key inclusion and exclusion criteria	Inclusion criteria: Aged 18 years or older. BMI (prior to weight loss) of ≥25 kg/m^2^. Verification of ≥5% of weight loss in the last 12 months and remain 5% below their highest weight. Ability to use a smartphone and have access to smart phone, tablet or computer with internet access and Wi-Fi. Ability to use standing scales for weight measurements and must not be over 150 kg (the scale limit 158 kg) Exclusion criteria: Inability to give informed consent. Lost weight due to illness or surgical procedures, including bariatric procedures. Pregnant or breastfeeding. Involvement in another research intervention study that confound with the aims of NoHoW (excluding local health interventions and weight management services). Inability to follow written material or telephone conversations in the English, Danish or Portuguese language (depending on the centre). Diagnosed with an eating disorder (eg, anorexia nervosa, bulimia nervosa or purging disorder). Diagnosed with any condition that may interfere with increasing mild to moderate physical activities and which is unstable (ie, untreated or unable to be controlled by medication). Recent diagnosis with type 1 diabetes. Extensive planned travel, that is, moving away or long-term travel abroad (eg, more than 4 weeks). Living in the same household as existing participant in the trial.
Study type	Interventional, 2×2 factorial randomised controlled trial.
Date of first enrolment	20 March 2017
Target sample size	1600
Recruitment status	Completed (31/03/2018), no longer recruiting.
Primary outcome(s)	Weight (kg)
Key secondary outcomes	Body composition: (eg, fat mass and fat-free mass) and waist/hip ratio. Biomarkers: blood pressure, heart rate, cortisol (hair samples), HbA1c, cholesterol. Behavioural: physical activity, sleep and dietary intake. Psychological moderators and mediators of change for: self-regulation and motivation (eg, action planning and coping, self-efficacy); CBS-emotion regulation (eg, weight focused self-criticism, five dimensions of mindfulness); stress management (eg, perceived stress scale, depression, anxiety and stress); and quality of life and well-being. Process evaluation Cost-effectiveness analysis

BMI, body mass index; ICT, information and communications technology.

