### Assessments

The primary outcome is change in weight (kg) between baseline and 12 months (primary endpoint). Follow-up measures for WLM are completed at month 18 for comparability with other longitudinal studies.^22^ All physical measurements are taken after a 10–12 hour overnight fast by trained research staff. Measures are taken at all four time points (baseline, 6, 12 and 18 months) except HbA1c, lipids and hair cortisol (baseline and 12 months only) and process evaluation measures (1, 3, 6 and 12 months only). The study schedule and information for all measures is in online supplementary file 2.

10.1136/bmjopen-2019-029425.supp2Supplementary data

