### Participant retention

Randomised participants are contacted at least 2 weeks before each visit and sent an email/text reminder. If participants deviate from planned assessments, three attempts are made to contact them by phone, email and a final written letter across 1 month. At least weight (primary outcome) is obtained if possible.

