### Data analysis

The 2×2 factorial design will be used in a model to investigate links between outcomes, and the extent of mediation or moderation by covariates. For continuous outcomes, linear regression models will be used. The effects of different treatment arms will be presented with 95% CI of coefficients and p values. For analyses that do not meet model assumptions, outcomes will be transformed prior to inferential comparisons. For categorical outcomes, logistic regression or categorical response models such as ordinal or multinomial regression will be used. Treatment effects will be presented as ORs, 95% CIs and p values. Missing values will be imputed using multiple imputation as part of an intention-to-treat (ITT) analysis.

To determine the mechanisms that underlie intervention efficacy, linear models are used to test whether the treatment (independent variable) causes a change in the potential mechanisms of change (mediators), which, in turn, cause a change in the primary and secondary outcomes (dependent variables). Models also investigate the effects of covariates that may moderate the effect of the interventions. Although a repeated measures/mixed model might potentially detect treatment effects not apparent when 6-month and 12-month outcomes are considered separately, our choice was driven by the primary role of the 12-month outcome. To be considered worthwhile, a WL or maintenance effect of treatment must be detectable at 12 months, whatever might happen during the time interval between then and baseline. Because of this, we chose to define the primary outcome and its analysis at 12 months alone.

For the primary outcome of weight, we intend to present results from an analysis of completers, of compliant participants and of the ITT population. Baseline and last observation carried forward are likely to be optimistic for dropouts, implying full WLM. So, for these dropouts, we will examine analyses which assume regain of all or a range of proportions of the weight lost since highest weight (in the 12 months before enrolment, for which all participants have provided evidence). Again, assuming return to baseline may be optimistic, but we do not have values at the time of greatest weight. Accordingly, we plan multiple imputation based on the imputed weight changes described above, using also centre and gender. This is not available for other health outcomes, such as HbA1c or blood pressure.

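### The rule excluding randomised participants who become ineligible is undefined; read literally it reaches outcome-related criteria and conflicts with the ITT analysis

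*Protocol article*

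**What the plan says.** Study recruitment describes consent before randomisation and then adds: "Participants are reconsented before each subsequent visit and excluded if they become ineligible". The later visits are the clinical investigation days at 6, 12 and 18 months. No subset of criteria is named, and the scope of exclusion is not given.

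The Participants section refers to Table 1 for eligibility. One inclusion criterion there is: "Verification of ≥5% of weight loss in the last 12 months and remain 5% below their highest weight". Table 1 also lists a body weight limit of 150 kg, a diagnosed eating disorder, and involvement in another intervention study that would confound the aims.

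Four other places bear on the point:

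- **Participants:** "Prior to randomisation, potential participants are asked to provide documented verification" of the qualifying weight loss.
- **Participant retention:** for people who deviate from planned assessments, "At least weight (primary outcome) is obtained if possible".
- **Data analysis, ITT:** "Missing values will be imputed using multiple imputation as part of an intention-to-treat (ITT) analysis". For dropouts, "we will examine analyses which assume regain of all or a range of proportions of the weight lost since highest weight".
- **Data analysis, mediation:** a categorical endpoint of maintenance against regain is the dependent variable.

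**The concern.** Entry criteria protect a trial up to randomisation. Rechecking them afterwards, and removing people who fail, breaks the comparison of the groups as randomised whenever failing is related to the outcome or the treatment. Here the link can be direct. The primary outcome is weight change at 12 months, and staying 5% below highest weight is a threshold on that same weight. Passing 150 kg, receiving an eating-disorder diagnosis or joining another intervention study can also follow from regain or from the allocated programme.

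If regainers were removed, more would go from the less effective arm. Those left in each arm would look like better maintainers, and the difference between arms would shrink. The research team is unblinded (Randomisation and blinding), so an undefined rule could also be applied unevenly between arms.

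**Working it through.** **1. The plan's own figures.** Power calculations gives 1.5 kg as d = 0.25, so SD = 1.5 / 0.25 = 6 kg. With two-sided alpha 5% and 80% power (the 5% is stated for HbA1c and assumed here for weight), n per arm = 2 × (1.96 + 0.84)² / 0.25², which is 252 after rounding up, against 250 stated. Power at 250 per arm is 79.8%. For dropout, 1600 × 0.62 = 992 against 1002 stated. These figures reproduce and are not in dispute. The 38% dropout allowance has no separate component for exclusions after randomisation.

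**2. The sections side by side.**

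| Section | Implication for a randomised participant who no longer meets Table 1 |
|---|---|
| Study recruitment | Excluded; scope not stated |
| Participant retention | Weight still sought if possible |
| Data analysis, ITT | Kept, with missing weight imputed |
| Data analysis, mediation | Regain is an outcome category, so regainers must be present |

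The first row cannot be followed literally together with the other three.

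**3. What the literal reading would do to the estimate.** Let H be highest weight, L the percentage lost at entry and C the change from baseline to 12 months. A participant still meets the 5% condition if baseline + C ≤ 0.95H, that is, if C ≤ H(L − 5)/100.

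*Hand check.* Assume H = 90 kg, L = 10% for everyone, and mean change +2 kg in control and +0.5 kg in intervention. The threshold is 90 × 5/100 = 4.5 kg. The mean of those kept is μ − σφ(z)/Φ(z), with z = (4.5 − μ)/6.

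- Control: z = 0.417, Φ = 0.662, φ = 0.366; kept mean = 2 − 6 × 0.553 = −1.32 kg; 34% excluded.
- Intervention: z = 0.667, Φ = 0.748, φ = 0.319; kept mean = 0.5 − 6 × 0.427 = −2.06 kg; 25% excluded.
- Difference: about 0.75 kg instead of 1.5 kg.

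*Simulation with spread in prior loss.* From the article: SD 6 kg and a true difference of 1.5 kg. Assumed: H = 90 kg; L = 5% plus a gamma variable (shape 1.5); mean L and mean control change as shown. Anyone above 95% of highest weight at 12 months is dropped, with no imputation. Power starts from 250 per arm before exclusions.

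| Mean L | Control change (kg) | Excluded, control / intervention | Estimated difference (kg) | Power |
|---|---|---|---|---|
| 8% | 0 | 34% / 26% | 0.83 | 41% |
| 8% | +2 | 46% / 37% | 0.73 | 32% |
| 8% | +4 | 58% / 49% | 0.65 | 24% |
| 10% | 0 | 26% / 20% | 0.97 | 50% |
| 10% | +2 | 37% / 29% | 0.91 | 43% |
| 10% | +4 | 48% / 40% | 0.84 | 34% |
| 12% | 0 | 21% / 15% | 1.08 | 57% |
| 12% | +2 | 30% / 23% | 1.02 | 50% |
| 12% | +4 | 40% / 33% | 0.99 | 44% |

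The range is 0.65-1.1 kg. With mean prior loss of 15% it is milder, at 1.12-1.19 kg.

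**4. Milder readings.** Assumed in addition: 6-month SD 4.5 kg and correlation 0.75 with 12 months, over mean prior losses of 8-12%.

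- Criterion applied at 6 months only, complete cases: about 1.2-1.3 kg (lowest 1.14 kg).
- Excluded participants imputed at full regain to highest weight, at either timing: about 1.0-1.5 kg.

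**The case against.** A reader might infer that the trial re-applied all entry criteria at every visit, removed regainers and so defeated its ITT analysis. The article does not support that, and the counter-arguments are strong.

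- No section says that regain leads to exclusion. Verification of the loss is placed before randomisation.
- The 5% condition is part of a compound criterion about the previous 12 months. Re-applied in full at 12 months, it would also exclude perfect maintainers, whose loss would by then lie outside that window. It reads as an entry condition.
- The mediation analysis and the assumptions for dropouts both presuppose that regainers are analysed. Nothing says that excluded participants leave the ITT set; they may be imputed, with regain assumed.
- Reconsent comes before the visit, so that visit's clinic weight would not yet be known. A participant already weighed at 12 months has the primary outcome.

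All of this stands. It makes the complete-case figures a worst case and not a description of the plan. It does not remove the defect. The sentence is stated and unqualified, and Table 1 is the only eligibility list to read it against. The other criteria that can arise after randomisation remain in reach even if the 5% condition was never rechecked.

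The article also intends for weight that "we intend to present results from an analysis of completers, of compliant participants and of the ITT population", without saying which result decides. That is a separate matter, commonly left to the SAP, and is not part of this point.

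**Conclusion.** The point holds as an undefined exclusion rule after randomisation that conflicts with the ITT analysis, with the retention aim and with regain as an analysed endpoint. Whether it caused any bias depends on how it was applied, which the article does not show.

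If the 5% criterion was used, the direction is towards no difference in every scenario examined. From 1.5 kg, the estimate would be about 0.65-1.1 kg (complete cases, applied at 12 months), about 1.2-1.3 kg (applied at 6 months only), or about 1.0-1.5 kg (excluded participants imputed as full regain). Only the SD and the true difference come from the article. Highest weight, prior loss, regain and the 6-month SD and correlation are assumptions. Exclusions under the other criteria were not quantified, because the article gives no basis for their frequency.

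**What to change.** Replace the sentence in Study recruitment with: *Eligibility criteria apply at baseline only for the purposes of follow-up and analysis; a randomised participant who later meets an exclusion criterion remains in follow-up, weight is sought at 6, 12 and 18 months while consent continues, and all randomised participants are analysed as allocated in the ITT analysis.* Reconsent can stay as a separate sentence.

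If anyone was excluded under the present rule, include any weights already collected and report the number and reason by arm. If nobody was, say so.

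Whether the intervention itself stops for such a participant is a clinical matter. The sections need to be reconciled on it, separately from follow-up of weight.

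The cost is one sentence and, if there were exclusions, a short table by arm. No extra participants are needed, and the sample size calculation is unchanged.

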### Public involvement

Members of the public that matched the study’s inclusion criteria at the three trial centres were consulted via a survey to inform the recruitment strategies, trial conduct, questionnaires, assessment of burden and reviewing or testing the intervention content at all trial centres. During the toolkit development stage, the public were involved in two ways. First, a panel of 10 people, matching the trial criteria, tested the toolkit V.1 written in English for 1 month in the UK. A mixed methods approach was used for the analysis of the data assessing technical maturity of the intervention and user experiences, through questionnaires (quantitative data), interviews (qualitative data), TK usage log data and data from wireless scales and activity trackers (Fitbit). These analyses will be published in a separate paper. The results were used to inform toolkit V.2. Toolkit V.2 was then tested for 18 months using a panel of 30 people (10 in each centre) starting 3 months before the launch of the trial. Trial staff regularly collaborated with the panel to identify technological glitches that could be corrected early on so as not to impact on the main trial participants.

### Interventions

The toolkit is a mobile-enabled website, delivered as a portfolio of embedded tracking technologies, mini-apps and web resources (figure 2) accessible via computer, tablet and mobile phone. The tracking technologies consist of an activity and sleep tracker (Fitbit Charge 2) and smart wireless body weight scale (Fitbit Aria). Participants were asked to wear the Fitbit Charge 2 at all times and to weigh themselves ≥twice weekly. All arms include instructions for self-weighing and use of activity trackers. Arms 2 and 4 include individualised weekly feedback about weight trajectories. Guidance for complex interventions was followed during the toolkit development specifying the intervention logic models and theory-driven behaviour change techniques,^50^ which will be detailed in a separate publication.

**Figure 2 F2:**
[figure not shown]
Toolkit example (arm 4).

#### Arm 1 (active control, self-monitoring, only)

The active control arm includes a toolkit dashboard containing weight, steps and sleep graphs using data from the Fitbit devices, healthy eating and mood data (self-scored on a five-point scale), a diary to populate with notes from these five tiles and a help tile. The content is generic and does not relate to any theoretically informed, evidence-based behaviour change approaches.

#### Arms 2–4

After randomisation, participants received standardised training from researchers during the first CID, specific to their arm allocation. Trial arms 2–4 include the same components as arm 1 but participants also receive a personal virtual road map (the ‘NoHoW Journey’) with intermediate destinations represented in that map by circles, each comprised of evidence-based theoretically informed thematic modules targeting self-regulation and motivation (arm 2), emotion regulation (arm 3) and combined self-regulation and emotion regulation (arm 4). Arm 4 includes the same number of thematic modules as arms 2 and 3. Each weekly module opens into submodules. The active intervention involves 18 weekly sessions delivered throughout a 6-month period. Users are encouraged to complete ≥1 submodule per week following the sequence in the road map, consisting of videos/audios, interactive graphs, text, images, questionnaires and mini-apps. Weekly arm-specific emails are sent during the active 6-month intervention phase, which provide WLM information, suggestions and reminders to visit specific content. The toolkit automatically sends an email notifying participants to slow down if they complete three sessions ahead of schedule. After 6 months, they are encouraged to revisit the toolkit for a further 12 months at their discretion.

Individualised feedback is a component of the self-regulation and motivation arms (arms 2 and 4) automatically provided by the toolkit in response to the individual’s weight trajectory. Feedback is generated from the data extracted from three sources: (1) weight from the Fitbit Aria scales; (2) activity and sleep from the Fitbit Charge 2; and (3) user engagement with the toolkit, including day of the week. After daily usage patterns are analysed, feedback is displayed in the toolkit consisting of one of a set of short statements (eg, “your weight management appears better when you are more active”).

#### Adherence

The toolkit sends automated weekly emails to participants to encourage engagement, prompt log-in and recommends sessions to complete (arms 2–4 only). The control group receives the same number of emails but with links to generic content (eg, topical diet/health information). Intervention adherence is continuously monitored by collecting information on the number of days since users last logged into the toolkit and the number of days since the last synchronisation between the Fitbit devices and data-hub. If no activity is detected after 21, 28 and 35 days, three attempts are made to contact participants by email. After 42 days of no activity, researchers telephone participants to resolve issues. Reasons for no activity are recorded.

### Assessments

The primary outcome is change in weight (kg) between baseline and 12 months (primary endpoint). Follow-up measures for WLM are completed at month 18 for comparability with other longitudinal studies.^22^ All physical measurements are taken after a 10–12 hour overnight fast by trained research staff. Measures are taken at all four time points (baseline, 6, 12 and 18 months) except HbA1c, lipids and hair cortisol (baseline and 12 months only) and process evaluation measures (1, 3, 6 and 12 months only). The study schedule and information for all measures is in online supplementary file 2.

10.1136/bmjopen-2019-029425.supp2Supplementary data

### Participant retention

Randomised participants are contacted at least 2 weeks before each visit and sent an email/text reminder. If participants deviate from planned assessments, three attempts are made to contact them by phone, email and a final written letter across 1 month. At least weight (primary outcome) is obtained if possible.

### Primary outcome

#### Change in weight (kg) at 12 months from baseline

Body weight (±0.1 kg) is measured using a Seca 704 s instrument (SECA, Germany) in participants wearing light clothing. Participants are asked to weigh themselves at least twice weekly, in the morning after voiding and before eating using the Fitbit Aria scales for 18 months.

### Secondary outcome measures

#### Body composition and height

Multifrequency whole bioimpedance spectroscopy is measured by ImpediMed (SFB7, Queensland, Australia), which measures impedance over a spectrum of frequencies for the estimation of body composition. Hanai mixture theory equations and standard resistivity constants^51^ are used to calculate fluid volumes to estimate total body water. Height (±0.1 cm) is measured with participants barefoot, using a Seca 704 s instrument (SECA, Germany). See online supplementary file 2.

